### **1.1.2 Research on molecular markers related to angiogenesis in NSCLC**

Tumor angiogenesis is intricately linked to tumorigenesis, progression, and metastasis. As tumors grow, angiogenesis is stimulated to supply nutrients, thereby promoting tumor expansion. Additionally, nascent blood vessels facilitate the dissemination of tumor cells, leading to distal metastases and further disease progression. Anti-angiogenic drugs aim to inhibit this process, thus disrupting the tumor's nutritional supply, impeding tumor growth, and reducing the likelihood of metastasis.

Among various pro-angiogenic factors, vascular endothelial growth factor (VEGF) is a key inducer of tumor angiogenesis, significantly promoting the proliferation and growth of endothelial cells. In lung cancer, VEGF is produced by tumor cells, and

elevated local concentrations of VEGF can upregulate the expression of its receptor, VEGFR, which is a critical mechanism driving angiogenesis in tumor tissues. VEGF facilitates the division and proliferation of vascular endothelial cells and stimulates neovascularization by binding to its primary receptor, VEGFR-2. Research indicates that VEGFR-2 is highly expressed in non-small cell lung cancer (NSCLC) and shows moderate to high expression in lung cancer tissues with lymph node metastases. This increased expression of VEGFR-2 is associated with enhanced tumor angiogenesis, accelerated tumor growth, and higher rates of metastasis, contributing to a poorer prognosis for patients.

### **1.1.3 Neoadjuvant studies of NSCLC and PD-1 inhibitors**

Nivolumab shows promising results in neoadjuvant therapy for lung cancer, as evidenced by the CheckMate 159 trial. Nivolumab monotherapy in a neoadjuvant setting has demonstrated a major pathological response (MPR) rate of up to 43%. With a current follow-up of 34.6 months, the median recurrence-free survival (RFS) has not yet been reached. However, the study indicates that patients achieving postoperative MPR have a lower rate of disease recurrence compared to those who do not achieve MPR. In the NADIM trial, which investigated neoadjuvant and adjuvant therapy with Nivolumab combined with chemotherapy for stage IIIA NSCLC, there was a significant improvement in pathological complete response (pCR) and MPR. The objective response rate (ORR) was 78.5%, all patients underwent R0 resection, and 93% experienced postoperative pathological downstaging. These findings suggest that neoadjuvant immunotherapy holds great potential in the treatment of lung cancer. However, further studies are necessary to fully explore and validate the efficacy and safety of neoadjuvant immunotherapy in this context.

## **1.2 Rational for the study**

With the widespread use of preoperative neoadjuvant therapy in the clinic, research on the application of antiangiogenic drugs in preoperative neoadjuvant therapy for locally advanced NSCLC continues to receive attention. Anlotinib hydrochloride is a multi-targeted receptor tyrosine kinase inhibitor with significant inhibitory activity against several kinases involved in angiogenesis and tumor proliferation. Specifically, it targets VEGFR1/2/3, FGFR1/2/3, and other tumor-related kinases such as PDGFR $\alpha$ / $\beta$ , c-Kit, and Ret kinases, offering a broad spectrum of inhibition that extends

to angiogenic kinases like Met and FGFR1/2/3. Additionally, Anlotinib exhibits potent inhibitory effects on several kinases currently under study, including Aurora-B, c-FMS, and DDR1. It is also effective against a variety of kinase mutants. By inhibiting tumor angiogenesis and promoting the normalization of blood vessels, Anlotinib disrupts the nutritional supply to tumors, thereby inhibiting tumor growth and reducing the likelihood of metastasis. It has been approved for the treatment of a variety of tumors in China, including locally advanced or metastatic NSCLC and SCLC with progression or recurrence after systemic chemotherapy, alveolar soft tissue sarcoma, clear cell sarcoma and advanced soft tissue sarcoma with progression or recurrence after chemotherapy. Its efficacy and safety have been observed in a number of clinical studies of first- and third-line treatment of lung cancer. In 2015, ASCO published a study of bevacizumab with chemotherapy in preoperative neoadjuvant chemotherapy for patients with lung adenocarcinoma, enrolling 42 patients with locally advanced stage IIIA (N2) and IIIB lung adenocarcinomas, which showed that the regimen was effective in increasing the rate of surgical resection and had a good safety profile. Neoadjuvant therapy for resectable NSCLC has become one of the recognized effective means. In neoadjuvant therapy, the main therapeutic tools include chemotherapy, TKI, radiotherapy, etc. The above studies have shown that the postoperative pCR is about 0-17%, and that the postoperative pCR is closely related to postoperative patient OS. Recently, immunotherapy has made impressive achievements in neoadjuvant therapy for lung cancer, and CheckMate 159 trial suggests that Nivolumab significantly improves PCR and MPR rates in preoperative neoadjuvant therapy, has better PFS, and is expected to improve OS. The existing neoadjuvant treatments of atalizumab in combination with chemotherapy and Nivolumab in combination with chemotherapy have achieved impressive results and high PCR. Therefore, in the neoadjuvant treatment of NSCLC, we attempted to carry out this neoadjuvant treatment of “quadruple combination (sintilimab, anlotinib combined with platinum-containing two-agent chemotherapy)”, and observed the efficacy and safety of this clinical program.

## **2. Research objectives**

To evaluate the efficacy and safety of neoadjuvant therapy for IIA-IIIB NSCLC by sintilimab and anlotinib in combination with chemotherapy.

### **3. Study Design**

#### **3.1 Description of research design**

This is a multicenter, prospective, open, single-arm clinical study to preliminarily explore the efficacy and safety of neoadjuvant sintilimab and anlotinib in combination with chemotherapy for IIA-IIIIB NSCLC.

#### **3.2 Primary endpoints**

**Efficacy:** Observe the pathological complete response (PCR) rate of resected tumor tissues in postoperative patients

**Safety:** According to NCI-CTCAE version 5.0, closely observe and record the incidence, severity, association, risk factors, measures taken and their regression of all adverse events (AEs); special attention should be paid to AEs of special interest (AESIs), which mainly include immune-associated pneumonia, immune-associated cardiomyopathy, immune-associated endocrine system disorders, hypertension, hemorrhage and proteinuria.

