### **3.5.3 drop-out/eliminate criteria**

1) Failure to administer the medication in accordance with the dosage, method and course of treatment specified in this research program.

2) Note: Cumulative discontinuation of more than two weeks in a dosing cycle is recorded as drop-out. Failure to use the medication in accordance with the provisions of the protocol resulting in the inability to conduct efficacy and/or safety evaluations;

3) Serious violation of the protocol: concurrent application of chemotherapeutic agents and/or treatment with modern Chinese medicinal preparations with anti-lung cancer indications while participating in this study.

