## **3.6 Treatment management**

### **3.6.1 Treatment plan**

Sintilimab (200mg fixed dose) iv, d1, q3w + anlotinib 10mg, po, qd1-14, q3w + platinum-doublet chemotherapy, evaluated after 3 cycles of combination therapy and discontinued for 3 weeks (21 days) followed by surgery, which was performed within 4-6 weeks (22-42 days) of the last dose. The time between each study dosing treatment was called a cycle.

A 3-week dosing and observation cycle was established for the trial. Patients who achieved effective disease control, including complete response (CR), partial response (PR), or stable disease (SD), continued treatment until surgery as per the trial protocol (Tumor Assessment Form, according to RECIST 1.1). For patients who experienced intolerable toxicity, disease progression, or requested to discontinue the drug, treatment was terminated. In cases of disease progression confirmed by imaging, the principal investigator (PI) should promptly review and understand the situation. If certain conditions are met, the patient may still be eligible for surgery with the PI's consent: the patient must be able to tolerate the surgery in terms of symptoms or quality of life, be fully informed and willing, and the surgery should be assessed by the treating physician (investigator) as potentially providing a survival benefit. If surgery is not deemed suitable, the patient may instead undergo standard radiotherapy treatment with the PI's consent.

| NSCLC                                                            |                                 |                                    |                        |
|------------------------------------------------------------------|---------------------------------|------------------------------------|------------------------|
| Drugs in the research                                            | Mode of administration          | Frequency                          | Duration of treatment* |
| Sintilimab
(200mg fixed dose)                                 | Intravenous,
over 30 minutes | Day 1
(one cycle every 3 weeks) | 9 weeks                |
| Anlotinib 10mg                                                   | Oral                            | Daily
(2 weeks on, 1 week off)  | 9 weeks                |
| Platinum-doublet
chemotherapy (guideline
recommended drug) | Intravenous                     | Day 1
(one cycle every 3 weeks) | 9 weeks                |

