### 3.6.2 Dose adjustment and discontinuation of administration

Anlotinib was discontinued if patients developed haemoptysis. For other grade  $\geq 3$  treatment-related adverse events (TRAEs), anlotinib was reduced to 8 mg, and the dose of chemotherapy was reduced by 25.0% of the last dose. Dose modification of sintilimab was prohibited. Patients experiencing intolerable adverse events that led to a delay or discontinuation of one drug continued treatment with the remaining study drug. Treatment continued until intolerable toxicity occurred or consent was withdrawn. Those who developed progressive disease were permitted to undergo surgery or receive SOC-CRT at the investigator's discretion.

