### **5. Statistical methods**

#### **5.1 Analysis variables**

##### **5.1.1 Main indicators**

1) Pathologic complete response (pCR) rate: The pCR rate is defined as the proportion of subjects with no residual invasive cancer on hematoxylin and eosin-stained slides of resected lung specimens and lymph nodes after completion of neoadjuvant therapy. For pathological assessments, primary lung tumors and lymph node specimens were staged using the AJCC criteria (8th edition). Residual viable tumor percentage in primary tumors was determined from routine hematoxylin and eosin-stained specimens. Tumors with no residual tumor cells (ypT0N0M0) were classified as having pCR. Pathological downstaging was defined as a reduction in ypTNM stage post-treatment, with no new lesions or progression of existing lesions.

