## **5.3 Determination of sample size**

Number of subjects: n=45

The sample size calculation used Simon's two-stage maximum value design. Based on the Checkmate-816 trial, the minimum pCR rate was set at 25%, and the expected pCR rate was 45%. Assuming a type I error rate ( $\alpha$ ) of 0.05 and a type II error rate ( $\beta$ ) of 80%, a sample size of 41 patients was needed. Seventeen patients were enrolled in stage 1. If more than 5 patients achieved pCR, the trial proceeded to stage 2; otherwise, the trial was terminated.

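### The primary pCR rate is defined among operated patients, the two-stage rule counts enrolled patients, and unresected patients are given no outcome

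*Protocol*

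**What the plan says.** Section 3.2 gives the primary efficacy endpoint as "Observe the pathological complete response (PCR) rate of resected tumor tissues in postoperative patients". Section 5.1.1 speaks of a proportion of subjects, but assesses it on "resected lung specimens and lymph nodes after completion of neoadjuvant therapy".

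Section 5.3 uses a different population for the decision: "Seventeen patients were enrolled in stage 1. If more than 5 patients achieved pCR, the trial proceeded to stage 2". It gives a minimum pCR rate of 25%, an expected rate of 45% and a required total of 41. Planned recruitment is 45 (3.4 and 5.3). No final boundary is printed.

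The protocol expects that some patients will not be operated on. For imaging-confirmed progression, 3.6.1 says: "If surgery is not deemed suitable, the patient may instead undergo standard radiotherapy treatment". Section 3.6.2 allows chemoradiotherapy as an alternative to surgery after progression, and the EFS definition in 5.1.2 includes inoperability as an event. None of these sections says how such a patient enters the pCR rate.

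On dosing interruptions, 3.5.3 states: "Cumulative discontinuation of more than two weeks in a dosing cycle is recorded as drop-out". Under 3.6.2, a patient for whom one drug is delayed or stopped because of intolerable adverse events "continued treatment with the remaining study drug". The protocol does not say whether a drop-out record affects the pCR analysis.

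**The concern.** Under 3.2, whether a patient is in the denominator depends on whether that patient reached surgery. An unresected patient cannot have a pCR, so leaving such patients out can only raise the rate, or leave it at zero. The rate then answers a narrower question: how often pCR occurs among those for whom treatment went well enough to operate.

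The trial has a single arm and is judged against a fixed 25%. With no control group passing through the same selection, a gap between the population behind 25% and the population in the denominator goes straight into the conclusion. The protocol supports two denominators for the same endpoint. In an open-label trial, the choice between them could be made after it is known who was resected.

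**Working it through.** **Inputs from 5.3.** Null rate 0.25, alternative 0.45, alpha 0.05 (taken as one-sided), stage 1 of 17 patients continuing if more than 5 have pCR, total 41. The section prints 80% as the type II error; I read it as power.

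**Reproducing the design.** For a pCR probability p, the chance of declaring success is

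P(p) = Σ from x = 6 to 17 of Pr[Bin(17, p) = x] × Pr[Bin(24, p) ≥ 15 − x],

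where 24 = 41 − 17. The cut-off of 15 is derived: with a final rule of at least 15 of 41, P(0.25) = 0.0498 and P(0.45) = 0.803. This matches the stated alpha and power, so the printed 17 and 41 reproduce.

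**Effect of the denominator on the rate.** Let f be the share of treated patients who are resected. If 25% of all treated patients have pCR, the rate among the resected is 0.25 / f. The protocol gives no f, so the values below are assumptions. The row 41/45 is the case in which the planned 45 yield exactly the 41 required.

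| Resected share f | 0.25 / f | P(0.25 / f), boundaries applied to resected patients |
|---|---|---|
| 1.00 | 25.0% | 0.0498 |
| 0.95 | 26.3% | 0.073 |
| 41/45 = 0.911 | 27.4% | 0.098 |
| 0.90 | 27.8% | 0.106 |

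On the same basis, the chance of passing stage 1 (more than 5 of 17) is 0.235 with all resected, 0.276 at 95% and 0.325 at 90%.

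**Counting enrolled patients instead.** If the 17 and 41 are enrolled patients and an unresected patient simply adds no pCR, the success probability per patient stays at 0.25 and the false-positive rate stays at 0.0498, whatever f is.

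**The price of that choice.** If the 45% target holds only among resected patients, the rate among all treated is 0.45 × f:

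- f = 1.00: 0.45, power 0.803
- f = 0.95: 0.45 × 0.95 = 0.4275, power 0.729
- f = 0.90: 0.45 × 0.90 = 0.405, power 0.640

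**The case against.** The strongest reply is that the only decision rule in the protocol, in 5.3, is worded in terms of enrolled patients. Read literally, it keeps the error rate at its nominal level. No section applies the boundaries to resected patients or replaces those not resected. This stands: a reader might infer that the trial's false-positive rate is inflated as planned, and the documents do not support that. They support a contradiction between the endpoint and the rule, with inflation on one of the two readings.

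The size also depends on what 25% means. Section 5.3 says only which trial it was based on, not the denominator. If 25% is a resected-only rate, the inflation disappears.

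A reader might also extend the table downwards, to 0.154 at 85% resected and 0.219 at 80%. Those figures need 41 resected patients, hence 41 / 0.85 ≈ 48 or 41 / 0.80 ≈ 51 enrolled, more than the planned 45.

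Two further inferences go too far. Section 3.6.1 mentions radiotherapy only for progression when surgery is unsuitable. It does not send patients with toxicity there, and both 3.6.1 and 3.6.2 allow surgery after progression, so some of these patients would stay in the postoperative denominator. Nor does any section remove a patient recorded as drop-out under 3.5.3 from the pCR analysis; leaving such patients out would raise the rate only if they responded less often than the rest.

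Finally, analysis sets are often left to the SAP, which is not shown here. That does not answer this point, because the conflict lies within the protocol and concerns its primary endpoint and its stopping rule.

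**Conclusion.** The inconsistency is established by the text: 3.2 and 5.1.1 point to operated patients, 5.3 to enrolled patients, and unresected patients have no assigned outcome. The rate as defined in 3.2 overstates pCR relative to all treated patients, by 1.3 percentage points at 95% resected and 2.8 at 90% when the true rate is 25%.

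The effect on the false-positive rate is conditional. It reaches 0.073 to about 0.10 only if the boundaries are applied to resected patients, if 25% is a rate among all treated patients, and if about 91% to 95% are resected. The final cut-off used for these figures is derived. The point should be settled before the result is interpreted, because it decides what the comparison with 25% means.

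**What to change.** - **3.2, 5.1.1 and 5.3:** use one primary denominator at stage 1 and at the end, namely all enrolled patients who received at least one dose. Count no surgery or no evaluable specimen as non-pCR. Report the resected-only rate as supportive.
- **MPR (3.3 and 5.1.2):** use the same denominator.
- **3.5.3:** state that a drop-out record does not by itself remove a patient from the pCR denominator. The protocol is silent here, so this is a clarification.
- **5.3:** state on which denominator the 25% and the 45% rest, and print the final boundary.

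The cost is wording, plus a somewhat lower reported pCR rate. If 45% proves to be a resected-only rate, power falls below the stated 80% as shown in the working, and the power figure should be restated. No new data are needed.

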#### **3.3 Secondary endpoints**

Observe the postoperative major pathologic response (MPR) rate, event-free survival (EFS) and overall survival (OS).

#### **3.4 Sample size**

The study was planned to be conducted in the Department of Thoracic Surgery of Tangdu Hospital of Air Force Medical University and the Third Affiliated Hospital of Chongqing Medical University, and a total of 45 patients were recruited.

#### **3.5 Inclusion and exclusion criteria**

##### **3.5.1 Inclusion criteria**

Subjects must meet the following inclusion criteria:

- 1) Age  $\geq 18$  and  $\leq 75$  years with a ECOG PS score of 0-1;
- 2) Subjects who can adhere to the study protocol;
- 3) At least one measurable lesion according to RECIST 1.1 criteria;
- 4) Stage IIA, IIB, IIIA, and IIIB NSCLC with histologically or cytologically

confirmed resectable NSCLC according to International Association for the Study of Lung Cancer and the 8th edition lung cancer TNM staging of American Joint Committee on Cancer Staging;

5) Participants must have a tumor tissue sample available for PD-L1 immunohistochemistry (IHC) and must submit a formalin-fixed, paraffin-embedded (FFPE) tissue block or unstained tumor tissue section and corresponding pathology report prior to enrollment. Tissue must be biopsy specimens from hollow-needle aspiration biopsies, excisions, or incisions. Fine-needle aspiration biopsies obtained by EBUS are insufficient for biomarker review and as a basis for randomization.

6) Tumor tissue samples must be fresh or obtained within 3 months prior to enrollment.

7) For all suspicious mediastinal lymph nodes evaluated by PET-CT or contrast CT findings, a pathological diagnosis was not necessarily required.

8) Good hematopoietic function, defined as absolute neutrophil count  $\geq 1.5 \times 10^9/L$  (not receiving granulocyte colony-stimulating factor supportive therapy), platelet count  $\geq 100 \times 10^9/L$ , hemoglobin  $\geq 90$  g/L; (no transfusion or no erythropoietin dependence within 7 days);

9) Good liver function, defined as serum total bilirubin  $\leq 1.5$  times the upper limit of normal (ULN); glutamic oxaloacetic transaminase (AST) and glutamic pyruvic transaminase (ALT) levels  $\leq 2.5$  times ULN in patients without hepatic metastases; and AST and ALT levels  $\leq 5$  times ULN in patients with documented hepatic metastases;

10) Good renal function, defined as serum creatinine  $\leq 1.5$  times ULN or calculated creatinine clearance  $\geq 60$  ml/min (Cockcroft-Gault formula); urine protein less than 2+ on routine urinalysis, or 24-h urine protein  $< 1$  g;

11) Good coagulation function, defined as an international normalized ratio (INR) or prothrombin time (PT)  $\leq 1.5$  times ULN;

12) Total lung function (e.g., FVC, FEV1, TLC, FRC, and DLco) capable of tolerating the proposed lung resection, as assessed by the surgeon;

13) For female subjects of childbearing potential, a negative urine or serum pregnancy test should be performed within 3 days prior to receiving the first dose (Cycle 1, Day 1);

14) If there is a risk of conception, male and female patients are required to use highly effective contraception and continue until at least 180 days after discontinuation of treatment.

### **3.5.2 Exclusion criteria**

- 1) Presence of locally advanced unresectable or metastatic disease;
- 2) Participants with known ROS1 fusion-positive or ALK translocations;
- 3)  $\geq$  grade 2 peripheral neuropathy;
- 4) Active autoimmune diseases (known or suspected). Type I diabetes, hypothyroidism requiring only hormone replacement therapy, skin disorders that do not require systemic therapy (e.g., vitiligo, psoriasis, or alopecia areata), or disorders that are not expected to recur in the absence of external stimuli are eligible for enrollment;
- 5) Those requiring systemic treatment with glucocorticoids ( $>10$  mg prednisone equivalent dose per day) or other immunosuppressive drugs within 14 days prior to randomization. Inhaled or topical steroids are permitted in the absence of active autoimmune disease;
- 6) Active hepatitis B/hepatitis C infection and known HIV infection;
- 7) Patients with prior chemotherapy or any other anti-tumor therapy;
- 8) Patients having received the following therapies in the past: anti-PD-1, anti-PD-L1, anti-PD-L2, or anti-CTLA-4 antibodies or any other antibody targeting T-cell co-regulatory pathways;
- 9) Patients who have been treated with anti-angiogenic drugs, such as anlotinib;
- 10) Patients with the presence of uncontrollable hypertension;
- 11) Presence of clinically uncontrollable pleural effusion or abdominal effusion;
- 12) Presence of clinically active diverticulitis, abdominal abscess, gastrointestinal obstruction;
- 13) Have received a solid organ or blood system transplant;
- 14) Diagnosis of other malignancies within 5 years prior to the first dose, excluding carcinoma that have been apparently cured, such as basal or squamous cell skin cancer, superficial bladder cancer, or carcinoma in situ of the prostate, cervix, or

breast;

15) Have active infection requiring systemic therapy;

16) Vaccination within 30 days prior to the first dose (Cycle 1, Day 1);

17) Patients with hemoptysis (>50 mL/day);

18) Patients whose tumors have invaded important blood vessels or who are at risk of hemorrhage during subsequent studies.

